## Abstract

**Background:**

Adults with high-functioning autism spectrum disorders (ASD) have difficulties in social communication; thus, these individuals have trouble understanding the mental states of others. Recent research also suggests that adults with ASD are unable to understand their own mental states, which could lead to difficulties in emotion-regulation. Some studies have reported the efficacy of cognitive-behavioral therapy (CBT) in improving emotion-regulation among children with ASD. The current study will investigate the efficacy of group-based CBT for adults with ASD.

**Methods/Design:**

The study is a randomized, waitlist controlled, single-blinded trial. The participants will be 60 adults with ASD; 30 will be assigned to a CBT group and 30 to a waitlist control group. Primary outcome measures are the 20-item Toronto Alexithymia Scale, the Coping Inventory for Stressful Situations, the Motion Picture Mind-Reading task, and an ASD questionnaire. The secondary outcome measures are the Center for Epidemiological Studies Depression Scale, the World Health Organization Quality of Life Scale 26-item version, the Global Assessment of Functioning, State-trait Anxiety Inventory, Social Phobia and Anxiety Inventory, and Liebowitz Social Anxiety Scale. All will be administered during the pre- and post-intervention, and 12 week follow-up periods. The CBT group will receive group therapy over an 8 week period (one session per week) with each session lasting approximately 100 minutes. Group therapy will consist of four or five adults with ASD and two psychologists. We will be using visual materials for this program, mainly the Cognitive Affective Training kit.

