### Assessments/measures

#### Primary outcomes

Our hypothesis is that CBT will help adults with ASD to understand their own and others’ emotions and thoughts and to exercise emotion regulation, by increasing their knowledge of ASD and self-awareness, especially their own strength and weakness related to ASD. Therefore, primary outcome measures will be the 20-item Toronto Alexithymia Scale, Japanese version (TAS-20) [26] scores at post-intervention to evaluate the ability to understand one’s own mind and the percentage of correct response on the Motion Picture Mind-Reading task (MPMR) [27] at post-intervention to evaluate the ability of understanding the minds of others. As other primary outcome measures, we will also adopt the Coping Inventory for Stressful Situations, Japanese version (CISS) [28] scores at post-intervention to assess coping skills during stressful situations and the ASD questionnaire scores at post-intervention to assess the knowledge about ASD and the attitude for ASD. These measures are described in greater detail below.

The TAS-20 is one of the most commonly used measures of alexithymia. Alexithymia is characterized by a difficulty in identifying and describing emotions and the tendency to minimize emotional experience and focus attention externally. This measure is a self-report one and consists of 20 items and three factors: difficulty in identifying feeling, difficulty in describing feeling, externally oriented thinking. Each items is rated from 1 (strongly disagree) to 5 (strongly agree) and the total score ranges from 20 to 100. The time required for this test is about 5 minutes.

The MPMR, developed by Wakabayashi and Katsumata [27], involves advanced theory of mind tasks. Tasks are based on the scenes from a television drama. A total of 41 video clips (each 3 to 11 seconds in length) are included from the television drama series, *Shiroi Kyotō* [The White Tower], which depicts malpractice in a famous Japanese medical school. The participant is asked to judge whether the word or phrase presented on the screen aptly describes the person in each scene. The time required for this test is about 15 minutes.

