The CISS determines the preferred coping style of an individual and assesses the relationship between the individual’s coping style and his or her personality. Its results are useful for treatment and intervention planning. The CISS measures three types of coping styles: task-oriented, emotion-oriented, and avoidance coping. This measure is also based on self-reports. The CISS consists of 48 items and each item is rated from 1 (not at all) to 5 (very much). The total score of each of the three coping styles ranges from 16 to 80. The time required for this test is about 10 minutes.

The ASD questionnaire that assesses the knowledge about ASD and the attitude to ASD was developed for this study. The questionnaire involved 10 knowledge-based questions (1 = true to 3 = not true) and five attitude-based questions (1 = disagree to 5 = agree) regarding ASD. The time required for this test is about 5 minutes.

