### Statistical methods

All analyses will be performed using SPSS 20 J (SPSS Inc., Chicago, IL, USA). All data will be analyzed under the intent-to-treat principle. For the primary outcomes, independent *t*-tests will be used to compare changes in scores between the pre-assessment and post-assessment periods between the CBT group and the waitlist control group. The primary outcomes will be analyzed controlling for potential confounds (for example, age, gender, IQ, and clinical characteristics) using regression models. Secondary outcomes will be analyzed using relevant tests at each assessment, controlling for possible confounds as described above. Subgroup analyses will be performed for any possible confounds to differentiate the efficacy of CBT at follow-up.

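### Four unranked primary instruments (at least six scores) are each t-tested with no success rule or multiplicity control; if any one significant score counts, the chance of a false positive is about 12–30%

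*Protocol article*

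**What the plan says.** The abstract lists the primary measures in one sentence: "Primary outcome measures are the 20-item Toronto Alexithymia Scale, the Coping Inventory for Stressful Situations, the Motion Picture Mind-Reading task, and an ASD questionnaire". Under Primary outcomes, the article presents the TAS-20 and MPMR first and then adds the other two: "As other primary outcome measures, we will also adopt the Coping Inventory for Stressful Situations, Japanese version (CISS"), together with the ASD questionnaire. All four are primary at post-intervention, and no order of importance is given.

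The number of scores behind each instrument is described in the same section:

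- **TAS-20:** three factors, but also a total, since "the total score ranges from 20 to 100".
- **MPMR:** one score, "the percentage of correct response on the Motion Picture Mind-Reading task (MPMR").
- **CISS:** "The CISS measures three types of coping styles: task-oriented, emotion-oriented, and avoidance coping". The range is given per style: "The total score of each of the three coping styles ranges from 16 to 80". No overall CISS score is defined, and no direction of benefit is given for any style.
- **ASD questionnaire:** "The questionnaire involved 10 knowledge-based questions (1 = true to 3 = not true) and five attitude-based questions", the latter on a 1–5 scale. No scoring rule says whether the two parts are combined.

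Statistical methods assigns the primary outcomes a two-sample t-test, which in the article's words "will be used to compare changes in scores between the pre-assessment and post-assessment periods between the CBT group and the waitlist control group". Regression with adjustment for potential confounders is also planned for these same outcomes. The section does not say which analysis decides. It states no significance level, no rule for how many primary outcomes must be significant, and no adjustment for testing several.

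**The concern.** A trial that sets out to show efficacy needs a definition of what result would show it. Here the article fixes several primary scores and a separate test for each, but not how the results combine into a conclusion. Read as written, any single nominally significant score can be reported as a positive primary result. That could be one CISS style, in whichever direction is afterwards described as better coping. A null intervention would then have several chances to look effective, and the reader of the final report could not tell a planned primary finding from a selected one.

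**Working it through.** **The plan's own figures.** The only sample-size arithmetic is 25 per arm, raised to 30 for dropout: 2 × 30 = 60, and 25/30 = 0.833, which allows 16.7% dropout. No significance level, power, effect size or SD is stated, so there is no error rate to reproduce.

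**Number of primary scores.**

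- Firm minimum: TAS-20 total (1) + MPMR (1) + CISS styles (3) + ASD questionnaire (1) = 6.
- With ASD knowledge and attitude scored separately: 7.
- With one score per instrument, which the article does not specify for the CISS: 4.

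**Assumptions, none of them in the article.** Each test is two-sided at 5%. Any one significant score counts as success. All scores share a common correlation ρ between 0 and 0.8. There is no true effect on any score.

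**Independent scores.** The chance of at least one false positive is 1 − 0.95^k:

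- k = 4: 1 − 0.8145 = 18.5%
- k = 6: 1 − 0.7351 = 26.5%
- k = 7: 1 − 0.6983 = 30.2%

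Counting only results in favour of CBT, each test contributes 2.5%, and the formula is 1 − 0.975^k: 9.6% (k = 4), 14.1% (k = 6) and 16.2% (k = 7).

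**Correlated scores.** These come from simulated two-sample t-tests with 25 per arm. Scores were generated as √ρ × shared part + √(1−ρ) × own part, with 200,000 runs and a Monte Carlo error of about 0.1 percentage point. Scores are oriented so that correlations are positive in the direction of benefit.

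| Scores | ρ | Any false positive | Favouring CBT only |
|---|---|---|---|
| 4 | 0.3 | 17.5% | 8.8% |
| 4 | 0.5 | 15.7% | 7.9% |
| 4 | 0.8 | 11.6% | 5.8% |
| 6 | 0.3 | 24.3% | 12.2% |
| 6 | 0.5 | 21.0% | 10.5% |
| 6 | 0.8 | 14.0% | 7.0% |
| 7 | 0.3 | 27.3% | 13.7% |
| 7 | 0.5 | 23.3% | 11.6% |
| 7 | 0.8 | 15.1% | 7.6% |

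The overall range is therefore about 12% (4 scores, ρ = 0.8) to 30% (7 independent scores), against 5% for a single test. In favour of CBT it is about 6% to 16%, against 2.5%. The additional regression analyses are not counted here and could add to these figures.

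**Power under control of the error.** Holm's first step for four scores uses 0.05/4 = 0.0125. The standardised difference detectable with 80% power, from the noncentral t distribution, is:

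- 25 per arm: 0.81 SD at 0.05 and 0.98 SD at 0.0125
- 30 per arm: 0.74 SD at 0.05 and 0.89 SD at 0.0125

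The second line applies if all recruited participants are analysed, as the stated intent-to-treat principle suggests.

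**The case against.** **The article condenses a fuller document.** The multiplicity procedure, the significance level and the subscale scoring may stand in a full protocol or SAP that is not shown. That is fair for the choice of procedure. It does not cover the design choice the article itself makes: four co-equal primaries, separately tested, in support of a single efficacy aim. What counts as success belongs with that choice.

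**The hypothesis is conjunctive.** The Objectives section joins the domains with *and*: understanding one's own and others' emotions, regulating emotion, and gaining knowledge of ASD. If every domain had to be significant, there would be no inflation. This stands as a possibility. But the sentence is a hypothesis, not a decision rule, and Statistical methods does not turn it into one. Equally, the article does not state that any one result suffices, so the error rates are conditional.

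**Two stronger readings are tempting.** A reader might infer that the chance of a false efficacy claim is 16–30% rather than 5%. The documents do not support that. Those percentages include false positives in favour of the waitlist, whereas a claim that CBT works needs a result in its favour. They also stop at a correlation of 0.5; at 0.8 the rate falls to about 12–15%. A reader might also count at least seven primary p-values. Seven requires splitting the ASD questionnaire, and no scoring rule in the article does so; the firm minimum is six.

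**Holm is not the only remedy.** One designated primary score, or a rule that all must be significant, would also control the error. This is correct, and the choice among them is the sponsor's.

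**Conclusion.** The concern holds in conditional form. The article fixes four unranked primary instruments, yielding six or seven scores, and gives no rule for turning their separate tests into a conclusion. If any one significant score suffices at two-sided 5%, the chance of at least one false positive is about 12–30%, and of one favouring CBT about 6–16% against 2.5%. These figures rest on the assumed significance level, the any-one rule, 4 to 7 scores, and a common correlation between 0 and 0.8. Within those ranges the rate stays at more than twice the nominal level. The arithmetic is secure. What is uncertain is which success rule the investigators would apply, and the article leaves that open on the question that decides the trial's main conclusion.

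**What to change.** Before outcome data are linked to allocation and analysed:

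1. Name one score per instrument with its direction of benefit: TAS-20 total, MPMR percentage correct, one CISS style, and one ASD-questionnaire score with its scoring rule.
2. Move the remaining scores to secondary.
3. Test the four with Holm's procedure at a family-wise two-sided 5%, with thresholds of 0.0125, 0.0167, 0.025 and 0.05 from the smallest p-value upwards.
4. Claim efficacy only for the domains that survive.

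A single designated primary score would also control the error, without splitting the 5%.

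Report the date of the decision. The Trial status section gives 88% of participants as already included and 68% of those as already tested at follow-up, and participants and therapists know the allocation. The choice therefore cannot be presented as made before data collection, and readers need to see when it was made.

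The change needs no new participants or visits, only wording in the plan. The cost is power at the first Holm step: the detectable effect rises by 0.17 SD with 25 per arm (0.81 to 0.98) or by 0.15 SD with 30 per arm (0.74 to 0.89).

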**Discussion:**

This trial will hopefully indicate the efficacy of group-based CBT for adults with high- functioning ASD.

**Trial registration:**

This trial was registered in The University Hospital Medical Information Network Clinical Trials Registry No. UMIN000006236.

## Background

Autism spectrum disorders (ASD) are a group of developmental disorders that include qualitative impairment in interpersonal communication as a core symptom. Even for an adult with high-functioning ASD, whose intellectual development is within the normal range, it is difficult to overcome difficulties in understanding the thoughts and emotions of others; this leads to impairments in interpersonal communication [1-3]. In recent years, studies have shown that an individual may not only find it difficult to recognize the emotions of others but also struggle with identifying one’s own emotions and matching the nature of those emotions with the appropriate strength and language given the current context; this can lead to difficulties in identifying or expressing their own mental states [4,5]. Some studies have shown that 50% of ASD adults have alexithymia, which is a personality construct characterized by a sub-clinical inability to identify and describe one’s own emotions [6,7]. This inability to identify or express one’s own mental states, coupled with a lack of emotion recognition, makes it even more difficult to establish mutual relationships. Failure to adapt to a group may become seriously affected and lead to interpersonal difficulties. Adults with ASD often present with one or more co-morbid disorders, such as anxiety or depression [8,9]. In many cases, a combination of mood disorders and anxiety arises due to chronic stress within a group. Hence, the treatment of patients with underlying ASD is a major issue for the mental health field. Even if symptomatic treatment is successful in relieving psychiatric symptoms, adults with ASD still find it difficult to adapt to society due to interpersonal communication difficulties. Recent research has also suggested that there are many adults with undiagnosed ASD among individuals who receive treatment for other psychiatric disorders. Many are diagnosed with ASD in adulthood without noticeable ASD symptoms during childhood [10].

Cognitive-behavioral therapy (CBT) interventions are being implemented within small group or individual therapy, with the aim of improving the regulation of emotions associated with ASD difficulties [11-15]. Sofronoff and colleagues [12] examined 71 children, aged 10 to 12 years, diagnosed with Asperger’s syndrome (AS). In some cases, the children’s parents were randomly assigned to one of three conditions (child-only intervention, child and parent intervention, and waitlist control). Small-group CBT was carried out, and the results for the three groups were compared among the three groups. Each of the intervention groups contained three participants, matched on sex and age. Two graduate student therapists conducted CBT for each group. There were 23 participants, over eight groups, in the child-only intervention group. Although there was no direct parental involvement, activities were explained after the sessions, and parents were instructed to have their children perform tasks at home. There were 25 participants, over nine groups, in the child and parent intervention condition. The interventions for the children in this condition were the same as those in the child-only intervention condition, with one psychotherapist for each group, which also included two parents. Twenty-three individuals were assigned to the control group. Six 2 hour sessions, during which participants studied how to be emotionally aware and use appropriate methods for coping with emotions, were conducted over 1 week. Results were examined via children’s self-assessments using the “James and the Maths Test”, a story describing anxiety about a math test. The parents also completed an assessment using the Spence Child Anxiety Scale and Social Worries Questionnaire–Parent. These assessments were performed at pre- and post-intervention, and also during a follow-up session (6 weeks later). A significant intervention effect was observed when both children and parents took part in the intervention; the child-only intervention was the next most effective treatment. Furthermore, a randomized comparative trial conducted by Sofronoff and colleagues [13] revealed similar results for a small-group CBT intervention to help with anger control. Based on the efficacy of the emotion-regulation which these studies showed, the Cognitive Affective Training Kit (The Cat-kit) was developed [16]. It is designed to help individuals with ASD become aware of how their thoughts, feelings and actions all interact and, in the process of using the various visual components, they share their insights with others.

### Objectives

The purpose of this study is to investigate the efficacy of group-based CBT for adults with ASD. Our primary hypothesis is that, through group-based CBT focusing on emotion-regulation and psychoeducation about ASD, adults with ASD can understand their own and others’ emotions and thoughts, exercise emotion-regulation, and increase their knowledge of ASD and self-awareness, especially of their own strengths and weaknesses related to ASD. A small-group adult CBT study protocol will be prepared with reference to previous CBT studies. As noted above, parent training, as well as other forms of intervention, can be carried out along with a child’s CBT. Thus, parents gain a greater understanding of ASD and the necessary modifications to a child’s environment, which is highly effective in enabling a parent being able to adapt to a child with ASD. However, unlike in children, adults with ASD need to understand more about their own strengths and weaknesses, as it is more desirable and practical that they are able to modify their own environment instead of his/her parents. Therefore, this study, which attempts to help improve social adaptation among adults with ASD, comprises two programs: (1) increasing the individual’s emotional awareness and allowing them to acquire appropriate coping skills, and (2) increasing self-awareness through ASD psychoeducation, by learning about the symptoms and biological cause of ASD and the individual’s strengths and weakness associated with it. These programs will be provided regularly, and the effects of these programs will be assessed.

## Methods/Design

### Trial design

This study is a randomized controlled trial. It follows a waitlist control, single-blinded (participants and psychologists who conduct the group-based CBT are not blinded and the assessors of all measures are blinded) design. The allocation of participants will be equal (1:1) across a CBT group (intervention group) and a waitlist control group. All assessment will be administrated by the blinded assessors at the enrolment, post-intervention, and at 12 weeks follow-up. The entire trial design is illustrated in Figure 1. First, an assessment for eligibility will be performed. For individuals who meet the inclusion criteria, a pre-assessment will be performed no more than 4 weeks before the treatment. After pre-assessment, participants will be allocated into the immediate treatment condition or the waitlist condition. After the completion of treatment, post-assessment will be performed within 4 weeks. After an additional 12 weeks, a follow-up assessment will be performed. The pre-assessment and intervention will be conducted at the Department of Child and Adolescent Mental Health, the National Institute of Mental Health, National Center of Neurology and Psychiatry, and the Department of Child Psychiatry, the University of Tokyo Hospital. The allocation and post- and follow-up assessments will be conducted at the Department of Child Psychiatry, the University of Tokyo Hospital.

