The CES-D is a self-report screening tool for depression and consists of 20 items. Each item is rated from 1 (absent) to 4 (five or more times a week), and the total score ranges from 0 to 60. The time required for this test is about 5 minutes.

The GAF is used by clinicians to make a global assessment of an individual’s adaptive level of functioning on a scale from 0 (poor) to 100 (good). The time required for this interview is about 30 minutes.

The WHO-QOL 26 is used to measure an individual’s subjective sense of wellbeing and quality of life, rather than determining the possible presence of an illness. The WHO-QOL 26 consists of 26 items and four domains: physical health, psychological health, social relationships, and environment. Each item is rated from 1 (poor) to 5 (good) and presented as an average score. The time required for this test is about 5 minutes.

It takes about 1 hour for the participant to fill out all of the questionnaires; therefore, they will be sent via mail to their home 7 to 10 days before the assessment date with careful consideration of the participants’ burden. During the pre-, post-, and follow-up assessments, the GAF and LSAS interviews will take about 30 minutes. The theory of mind tasks, MPMR (done on a PC) will take about 15 minutes.

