### Randomization

Enrollment and random allocation will be performed through central registration at the University Hospital Clinical Trial Alliance Clinical Research Supporting System (UHCT ACReSS) at the University of Tokyo. A minimization method will be used with sex as the allocation factor. A third party, who is not involved in this trial, will enroll participants after examining their eligibility and informed consent. Owing to allocation concealment, the random allocation sequence will be provided by UHCT ACReSS and will not be revealed to any researchers or staff until the end of the enrollment period. As this is a single-blinded trial, all assessments will be conducted by raters without knowledge of whether the participant is in the CBT or waitlist conditions.

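### The stated blinding of the assessors of all measures does not hold for three of the four primary outcomes, which are questionnaires completed by unblinded participants

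*Protocol article*

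**What the plan says.** Trial design describes a single-blinded trial in which "participants and psychologists who conduct the group-based CBT are not blinded and the assessors of all measures are blinded". The same section adds: "All assessment will be administrated by the blinded assessors at the enrolment, post-intervention, and at 12 weeks follow-up". Randomization says again that "all assessments will be conducted by raters without knowledge of whether the participant is in the CBT or waitlist conditions". The claim is therefore made three times and covers every measure.

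The abstract lists the primary outcomes: "Primary outcome measures are the 20-item Toronto Alexithymia Scale, the Coping Inventory for Stressful Situations, the Motion Picture Mind-Reading task, and an ASD questionnaire". Under Primary outcomes, the TAS-20 is described thus: "This measure is a self-report one and consists of 20 items and three factors". Of the CISS it says: "This measure is also based on self-reports". The ASD questionnaire has ten knowledge items and five attitude items, answered on true/not-true and disagree/agree scales.

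The end of Secondary outcomes says that the participant fills out the whole set of questionnaires, in about an hour, and that "they will be sent via mail to their home 7 to 10 days before the assessment date". It describes the GAF and LSAS as interviews and the MPMR as a task done on a PC.

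**The concern.** For a self-report, the participant is in effect the assessor, and the article says that participants are not blinded. A statement that the assessors of all measures are blinded cannot then be true of those outcomes. Blind collection or scoring of a completed form does not alter answers given by someone who knows the arm.

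The comparator makes this matter. One arm knows it has been treated and the other knows it is waiting, so expectation can move self-reports in the direction of benefit. If the blinding statement is carried into the results paper, readers will credit most of the primary outcomes with a protection they do not have.

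**Working it through.** The article gives no figure to reproduce here. The check is to classify each outcome instrument by who produces the score, using Primary outcomes, Secondary outcomes and Table 1, and to compare that with the blinding statements.

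| Instrument | Role | Who produces the score | Basis |
|---|---|---|---|
| TAS-20 | Primary | Participant | Explicit |
| CISS | Primary | Participant | Explicit |
| ASD questionnaire | Primary | Participant | Inferred from item format and from the participant filling out the whole set |
| MPMR | Primary | Participant's performance on a PC task | Explicit |
| STAI | Secondary | Participant | Explicit |
| SPAI | Secondary | Participant | Explicit |
| CES-D | Secondary | Participant | Explicit |
| WHO-QOL 26 | Secondary | Participant | Subjective measure; same inference as for the ASD questionnaire |
| GAF | Secondary | Interviewer | Explicit |
| LSAS | Secondary | Interviewer | Explicit; designed as self-report, given here as an interview |

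**Counts.** Primary outcomes: 3 of 4 are questionnaires completed by the participant, 1 of 4 is a PC task, and none is scored by a rater's judgement. All instruments: 7 of 10 are completed by the participant and 2 of 10 are interviewer-rated.

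**Cross-check on the mailed set.** Table 1 times for TAS-20, CISS, ASD questionnaire, WHO-QOL 26, STAI, SPAI and CES-D are 5 + 10 + 5 + 10 + 10 + 25 + 5 = 70 minutes. With the 5 minutes that the text gives for WHO-QOL 26, the total is 65. Both are compatible with about one hour. This fits all seven being in the mailed set but does not prove it for the ASD questionnaire.

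**Illustration of what is at stake.** Assume no true effect and a difference between arms of d standard deviations of the change score that comes from reporting alone. Statistical methods specifies independent t-tests on pre-to-post change. A two-sided 5% level is assumed. With n per arm, the noncentrality is d × √(n/2) on 2n − 2 degrees of freedom, and the rejection rate follows from the noncentral t distribution.

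| Assumed d | n = 30: noncentrality | n = 30: rejection rate | n = 25: noncentrality | n = 25: rejection rate |
|---|---|---|---|---|
| 0.2 | 0.775 | 11.9% | 0.707 | 10.7% |
| 0.3 | 1.162 | 20.8% | 1.061 | 18.0% |
| 0.5 | 1.936 | 47.8% | 1.768 | 41.0% |

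The sample sizes are the article's: 30 recruited per arm, 25 after allowing for dropout. The values of d are assumptions, since the article gives no basis for choosing one. The rates describe the consequence of unblinded self-report against a waitlist. Correcting the wording would not change them.

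**The case against.** The best defence is that nothing is hidden. The sentence that claims blinded assessors also says that participants are not blinded, the TAS-20 and CISS are labelled self-report, and the mailing is described. On this view assessors and raters are simply the staff who hand out and collect the measures, and the wording is loose. The first part stands: the article discloses participant unblinding, and a reader who infers that it conceals the weakness of a waitlist design goes too far. The second part does not rescue the statement, because the forms go out by mail and blind staff cannot take expectation out of the answers.

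It is also fair that the three primary questionnaires are not equally exposed. Ten of the 15 ASD questionnaire items are closer to a test. That this instrument is self-completed is an inference, and completion at home is implied by the mailing, not stated.

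Two stronger readings are tempting and are not supported:

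- A reader might take GAF and LSAS as protected against reporting bias. They are protected against rater bias only, because both draw on interviews with participants who know their arm.
- A reader might infer a leak of allocation from the statement that "The allocation and post- and follow-up assessments will be conducted at the Department of Child Psychiatry, the University of Tokyo Hospital". Randomization describes a central system, a third party who enrols, and a sequence withheld from researchers and staff until enrolment ends. A site and a central system are compatible, and nothing says that allocation is visible to the raters.

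**Conclusion.** The blinding statement is wrong as written. It does not hold for three of four primary outcomes (two explicitly self-report, one by inference) or for 7 of 10 instruments overall. Because it is a positive statement in the text, and not a detail left to a fuller document, the condensed format of an article does not excuse it.

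The error lies in the scope of the claim and in what the trial may conclude from these outcomes. It is not concealment, and it does not show that the self-report results will be biased by any particular amount. The rejection rates are illustrations under assumed shifts. Among the primary outcomes, the MPMR, scored as correct responses, is the least open to reporting bias, although the person performing it also knows the arm.

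**What to change.** 1. In Trial design and Randomization, limit the blinding statement to the GAF and LSAS raters and to the staff who administer the MPMR.
2. Describe the TAS-20, CISS, ASD questionnaire, STAI, SPAI, CES-D and WHO-QOL 26 as unblinded participant-reported outcomes compared with a waitlist. Confirm that the ASD questionnaire and WHO-QOL 26 belong to the mailed set.
3. State in the analysis section that a positive result found only on these questionnaires will be reported as unblinded evidence.
4. Name the MPMR as the primary outcome least open to reporting bias, and note that blinding of GAF and LSAS guards against rater bias only. The knowledge items of the ASD questionnaire may be noted as less open to expectation than the attitude items.

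The cost is wording and a less favourable claim. No outcome, test, sample size or procedure changes, so the correction is still possible with 88% of participants already included (Trial status). It should be made before results are reported.
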